##### Wellbeing outcomes

As discussed above, it is anticipated and consistent with the intervention theory of change, that pupil wellbeing will improve as a result of exposure to the WSS Review. Pupil wellbeing is measured using the self-report Strengths and Difficulties Questionnaire (SDQ) for 11–17-year-olds. The SDQ provides a measure of the psychological adjustment of the respondent (or their psychopathology) [11]. The SDQ measure of interest is the ‘total number of difficulties’ score.

#### Baseline measures

Baseline measures will be used for adjusted analyses of trial data for both primary and secondary outcomes. Where possible for each primary and second outcome, a pre-randomisation measure on the same outcome will be obtained in order to form a baseline covariate in the relevant analyses.

##### Attainment

For outcomes in English and Mathematics at GCSE, regardless of whether defined in terms of grade or marks, a baseline covariate will be derived from the raw test scores in Reading and Mathematics at Key Stage 2 (KS2; national tests at 11 years), as appropriate, collected directly from schools before randomisation for each enumerated pupil in years 8 and 9 at September 2020.

##### Attendance and exclusions

Analysis of attendance and exclusions outcomes will be adjusted on the basis of baseline measures of attendance for the school year 2019/20 (noting the shortening of the school year due to the Covid-19 pandemic and the closure of schools). These measures relate to the period of time prior to randomisation, which will take place in June 2021. The covariate will be derived by summing the total number of absences (both authorised and unauthorised) for each pupil for the school year 2019/20.

##### Wellbeing outcomes

An SDQ will be administered to each enumerated pupil at baseline in Years 8 and 9 in May 2021, prior to randomisation. For each pupil that completes the baseline SDQ, we will derive a baseline total difficulties score to be used in the adjusted analysis as a covariate.

##### Additional baseline data items

In addition to the ‘pre-test’ baseline data items mentioned above, further items will be collected at baseline for use in the analysis. These are as follows:
Date of birthSexFSM statusSEND (ECHP or ‘support’)Primary identification of need (e.g. SEND-related need)Current class for English (at September 2020)

The analysis discussed below provides for the estimation of effects through (a) an unadjusted analysis, (b) an analysis adjusted for the inclusion of a baseline measure on the dependent variable as a covariate at the pupil level only and (c) full adjusted specification which includes a baseline measure of the dependent variable entered as a covariate at the pupil and school levels as well as further covariates for month of birth, sex and FSM. All specifications will include a region indicator that reflects randomisation by region. Further, the SEND indicator is required in order for the primary analysis to be performed on the subset of the two cohorts years 8 and 9 that are designated either ‘support’ or ‘ECHP’ at the point of randomisation. An FSM indicator is required in order for subgroup analysis to be performed.

### Participant timeline {13}

*At September 2020 **Enrolment paused and restarted during this period due to the COVID-19 pandemic

### Sample size {14}

Table 2 sets out the assumptions upon which we have based sample size calculations. It states the relevant minimum detectable effect sizes [12] associated with the primary analysis (SEND designated pupils only), analysis for all pupils (the sample upon which many secondary outcomes will be estimated) and subgroup estimates for pupils ever in receipt of Free School Meals (FSM; the main subgroup analysis).

**Table 2 Tab2:** Sample size calculations (calculated using PowerUp!^a^)

	All pupils	SEND pupils	FSM pupils
**Minimum Detectable Effect Size (MDES)**	0.19	0.20	0.19
**Pre-test / post-test correlations**			
Level 1 (pupil)	0.70	0.70	0.70
Level 2 (class)	n/a	n/a	n/a
Level 3 (school)	0.32	0.32	0.32
**Intracluster correlations (ICCs)**			
Level 2 (class)	n/a	n/a	n/a
Level 3 (school)	0.20	0.20	0.20
**Alpha**	0.05	0.05	0.05
**Power**	0.80	0.8	0.8
**One-sided or two-sided?**	Two	Two	Two
**Average cluster size**	180	25	42
**Number of schools**			
Intervention	80	80	80
Control	80	80	80
Total	160	160	160
**Number of pupils**			
Intervention	14,400	2000	3360
Control	14,400	2000	3360
Total	28,800	4000	6720

^a^PowerUp! https://www.causalevaluation.org/power-analysis.html

The size of the anticipated sample available for this trial is influenced by the following factors:
The costs to the developer of working with schools and the available programme budget which determines the maximum possible size of the intervention group.The number of schools that the developer could reasonably be expected to recruit in the time available based on our experience of recruiting secondary schools to other similar EEF-funded studies.The average size of schools.The likely proportions of pupils within schools that are SEND and have ever qualified for free school meals.

In addition, our sample size calculations are based on a number of further assumptions in relation to:
The correlation between KS2 English raw scores and GCSE English marks.The intraclass correlation coefficient at the school level.Whether information on the class that individual pupils were in at randomisation for the teaching of English language is available, and if available, is reliable.

In addition to these factors, schools will be assigned to intervention and control groups on a 1:1 basis. Statistical tests will be conducted on the basis of two-sided tests of statistical significance with standard assumptions made regarding types I and II statistical error rates (5 and 20% respectively).

At the outset of the study, the developers informed the research team that they had a budget to work with around 100 schools. This implied the need to recruit some 200 schools to the trial such that subsequent to randomisation 100 schools would be assigned to the intervention. However, previous experience within the research team led to the conclusion that the developers would struggle to recruit 200 schools to this study in the time available. For example, the ‘Evaluating the effectiveness of Eedi formative assessment programme’ study, which also involved the recruitment of mainstream secondary schools to an EEF-funded trial, set out to recruit 180 schools, but despite the best efforts of the developers, only 158 schools agreed to take part in the trial [13]. Given this experience and the fact that the WSS Review will be more demanding on school resources in general, it was felt that 160 schools would be a reasonable but ambitious target that could be achieved by developers in the time available.

With an achieved sample of some 160 schools we can obtain estimates for the average number of pupils in a given focal-year-cohort, the number of pupils that are likely to be SEND as well as the expected number of pupils that had ever qualified for free-school-meals:
Based on previous studies we expect on average six classes in each year group in mainstream secondary schools and each class will comprise approximately 30 students.Thus we expect to find on average about 180 students in each year-group cohort per school (and that there are two cohorts per school).Drawing on national publicly available estimates, we expect that around 14% of pupils to be designated SEND [2]. This means that on average we expect to find 25 SEND pupils in each year-based cohort per schoolNearly a quarter of pupils in maintained secondary schools have qualified for FSM at some point in their school careers [14]. This means we can expect around 42 pupils per cohort, per school to have been in receipt of FSM.

Given these estimates we anticipate that in some schools the numbers of pupils in our sample that will be both SEND and FSM will be very small. For this reason, the sample size estimates above are for all FSM, rather than SEND pupils that are also FSM. Likewise, as set out in the Statistical Methods section we do not propose estimating effects for that subgroup of SEND pupils that are also ever-FSM, due to anticipated small sample sizes.

We obtained an estimate of the correlation between KS2 Raw score for English and GCSE English language attainment from the analysis provided by the Education Endowment Foundation [15]. The assumption used for the intraclass correlation coefficient is 0.20 (proportion of the total variance at the school level), and though possibly conservative is the assumption used for many EEF-funded studies with GCSE attainment as a primary outcome.

Taken together these assumptions and other information lead to estimated minimum detectable effect sizes for the primary analysis of 0.20 of a standardised mean difference, and 0.19 for samples based on all pupils and those ever-FSM respectively. Given the prospects for school recruitment, the time frame over which recruitment needed to take place and the available budget, assuming 80% power, these effects are the smallest true effects that would lead to results reaching levels of statistical significance at the 95% level. If we assume a standard deviation of around 50–60 marks in GCSE English language, an effect size of 0.20 translates, very approximately, into an average improvement among SEND students in intervention over control schools of around 10–12 Marks.

### Recruitment {15}

We initially identified that it would be necessary to recruit schools that had not previously engaged with WSS Review, thus requiring a substantial effort on behalf of the developer who was primarily responsible for recruitment. The developer was however in a strong position to do this, having a national reach and relationships with schools across all regions of England. Recruitment was supported by the trial sponsor (EEF) who have a similar national profile and established channels to aid the recruitment of schools for research. Stratification by region has allowed for efficiencies in recruitment thus far and will prevent unnecessary delays and achieve balance in the number of intervention and control schools in each region.

## Assignment of interventions: Allocation

### Sequence generation {16a}

Randomisation is stratified and will be performed regionally in five batches. Based on the sample size calculations, the developers aimed to recruit a minimum of 32 state secondary schools in each region, more if possible (although for the purposes of pairing an even number of schools is required in each region).

The randomisation process is the same for each region:
The authors will assign each recruited school a random number drawn from a uniform distribution in STATA v16 (a random number seed will be set and stored so that it can be retrieved at a later date).Schools will be ordered by the uniform random number on an ascending basis.Two groups of schools will be formed by splitting the ordered list of schools in half—the first group will be group 1, and the second group 0.Group 1 will be assigned to the treatment condition and group 0 will be assigned to the control condition.

### Concealment mechanism {16b}

Allocation concealment will be achieved as randomisation will be conducted by computer, with school identifiers unknown to the research statistician running the randomisation script. Assignment status will be made known to all enlisted schools in June 2021.

### Implementation {16c}

The researchers will assign schools to the intervention by the procedure outlined above (sequence generation).

## Assignment of interventions: Blinding

### Who will be blinded {17a}

There are no specific measures for blinding. However, whilst the group assignments will be known to the researchers, data collectors, developers, SENDCos and other school staff, it is unlikely that pupils will be aware of the implementation of the intervention as distinct from other school activities.

### Procedure for unblinding if needed {17b}

The design is open label so unblinding will not occur.

## Data collection and management

### Plans for assessment and collection of outcomes {18a}

All data outcome and baseline data collection is being undertaken by FFT, a non-profit organisation “focussed on providing accurate and insightful information to schools which enables pupils to achieve their full potential and schools to improve” [16]. Many schools in the UK use FFT’s Aspire reporting and data tool, and FFT therefore have direct access to the majority of data to be collected in the trial. Where a trial school uses Aspire, data will be sent to the school by FFT for validation before being returned to FFT by the school. For schools that do not use Aspire, FFT will directly request the data from the school. FFT have well-established internal processes for the quality assurance of data, and a second level of checks will be implemented by the research team.

#### Outcome data

In order to obtain attainment data, schools in the trial will be approached by FFT and asked for the marks and grades obtained by individual students at GCSE and provided to the school by exam boards. Data will be obtained at September 2023 (for pupils in year 9 at September 2020), and September 2024 (for pupils in year 8 at September 2020). The measures of Grade achieved by pupils will be equivalent to those available through the National Pupil Database (NPD).

At the point GCSE Grades are extracted from school data systems by FFT, absence and exclusion data will be obtained for pupils for the school year 2022/2023 for year 9 pupils (at September 2020) and the school year 2023/2024 for year 8 pupils (at September 2020).

FFT will also co-ordinate administration and data collection of wellbeing data, measured using the self-reported Strengths and Difficulties Questionnaire (SDQ) for 11–17-year-olds. The SDQ contains 25 items, 20 of which form four sub-scales: emotional symptoms, conduct problems, hyperactivity/inattention and peer problems. A score on each sub-scale is obtained and then the total number of difficulties derived from summing across the subscales. The additional five items form a separate prosocial behaviour scale which we are not intending to use in our analysis. The validity and reliability of the SDQ are discussed in Goodman & Goodman [17, 18].

Prior to randomisation (in June 2021), the SDQ will be administered online to the enumerated sample of pupils (overseen by teachers and teaching assistants) in both years 8 and 9 at baseline. The SDQ will again be administered at June/July 2022 (for year 9s) and June/July 2023 (for year 8s). The choice of timing of the follow-up SDQ measurements was informed by the need to avoid administering the instrument in year 11, when there are significant calls on teachers’ time and school resources in general. Doing so also provides the possibility of using well-being as a mediating variable in analyses of attainment [19], thereby taking into account the required temporal ordering of measurements to permit this.

#### Baseline data

FFT will also collect baseline data from Aspire and non-Aspire schools as the basis for adjusted analyses of trial data for both primary and secondary outcomes. Where possible for each primary and secondary outcome, a pre-randomisation measure on the same outcome will be obtained in order to form a baseline covariate in the relevant analyses.

This includes the following:
Raw test scores in Reading and Mathematics at KS2 for each enumerated pupil in Years 8 and 9 at September 2020.Absence and exclusion data for each pupil for the school year 2019/2020.Additional baseline data items (date of birth, sex, FSM status, SEND (ECHP or support), Primary identification of need, current class for English (at September 2020).

##### Linking records for primary, secondary and baseline measurements

Baseline data will be linked together to form the trial database using full name, date of birth, school Unique Reference Number (URN) and Unique Pupil Number (UPN). As stated, SDQs are administered separately at baseline (May 2021) and at a future point in time. Pupil level records generated from the SDQs will be linked to the baseline data records using UPN, full name and date of birth. Outcome data will also be linked accordingly.

### Plans to promote participant retention and complete follow-up {18b}

The researchers have started working with the developers to implement a communication strategy which emphasises to schools the importance of adhering to the trial. This was clearly communicated in the Memorandum of Understanding, to which all participating schools agreed. There is, however, a high chance that some schools recruited to the trial decide to withdraw, and this sample loss might both reduce the precision of statistical estimates and introduce bias. Where attrition occurs, steps will be taken in the analysis to test various assumptions regarding missingness and to assess consequences for bias and precision. Given the researchers’ experience of running other educational trials, we are not expecting a significant number of pupils to subsequently withdraw after enrolment is completed.

### Data management {19}

The Memorandum of Understanding (MOU) for schools and Data Sharing Agreement clearly specify the responsibilities of all parties with regard to the supply and processing of data. The process of data collection and quality assurance is described in the ‘Plans for assessment and collection of outcomes {18a}’ section above.

### Confidentiality {27}

Data will be transferred to the researchers via FFT’s secure transfer site. All research data will be held within a secure research area agreed with the University’s Head of Information Security. The information collected will be used for research purposes only and no information that can identify individuals will be used for any other purpose. Any personal data collected and held by Manchester Metropolitan University, nasen and FFT will be destroyed in accordance with the GDPR when it is no longer required, and no later than July 2025.

Any information identifying students will be given a unique ‘meaningless identifier’ prior to analysis in order to reduce risk. Data deposited in the EEF data archive (in the ONS SRS) will also include Pupil Matching References for any subsequent longitudinal matching which is not part of this trial. Therefore, data will only be released subsequently to ONS Accredited Researchers in an anonymised format.

### Plans for collection, laboratory evaluation and storage of biological specimens for genetic or molecular analysis in this trial/future use {33}

See Item 26b—there will be no biological specimens collected.

## Statistical methods

### Statistical methods for primary and secondary outcomes {20a}

Both primary and secondary analysis will follow the intention to treat principle.

#### Primary analysis

Focusing first on the primary analysis, statistical estimates of the effect of exposure on marks at GCSE English will be obtained from a hierarchical linear model (the estimator), in which pupils are clustered within schools. This model will be fitted to data for SEND pupils only. Three regression model specifications are proposed, where the standardised or equated mark for each pupil is the dependent variable^1^, and the regression models include the following covariates:
*Model 1*: binary intervention group indicator coded to ‘1’ if the school is assigned to the intervention ‘0’ otherwise, plus regional fixed effects (representing strata).*Model 2*: As above, with KS2 Reading raw score as a covariate expressed as a departure from the school mean for each pupil at the pupil level, and as a school average departure from the overall mean at the school level*Model 3*: As model 2, with additional covariates representing sex, month of birth, unauthorised absences in the year prior to randomisation and FSM variables.

The effect size, consistent with Hedges’ *g*, will be obtained from model 2, as set out in EEF guidance [20]. The effect size parameter is written:
$$ ES=\frac{\mu^T-{\mu}^c}{\sqrt{\sigma_i^2+{\sigma}_j^2}} $$

A sample estimate of *μ*^*T*^ − *μ*^*c*^, where *μ*^*T*^ is the mean of the outcome in the treatment group and *μ*^*c*^ the mean in the control group, is derived from the coefficient obtained on the binary intervention group indicator from model 2 above. The denominator $$ {\sigma}_i^2+{\sigma}_j^2 $$, where *i* indexes for the school and *j* the pupil, are the variances at the school and pupil levels respectively, such that the intraclass correlation coefficient is $$ {\sigma}_i^2/{\sigma}_i^2+{\sigma}_j^2 $$. A sample estimate for the denominator is obtained from the total unconstrained pooled variance as described in Hedges [20], who also provides an equation for the variance of the sample estimate for the effect size. Uncertainty will be assessed through computation of 95% confidence intervals and *p* values.

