**Attainment outcomes**					
**GCSE English language Mark (standardised)**	Linear hierarchical	Yes	Yes	• KS2 Reading raw score at pupil and school levels • Month of birth • Sex • FSM	Year 9
**GCSE English language Mark (standardised)**	Linear hierarchical	Yes	Yes	• KS2 Reading raw score at pupil and school levels • Month of birth • Sex • FSM	Year 8
**GCSE Mathematics Mark (standardised)**	Linear hierarchical	Yes	Yes	• KS2 mathematics raw score at pupil and school levels • Month of birth • Sex • FSM	Year 9
**GCSE Mathematics Mark (standardised)**	Linear hierarchical	Yes	Yes	• KS2 mathematics raw score at pupil and school levels • Month of birth • Sex • FSM	Year 8

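### KS2 Reading and Mathematics are both held for every pupil, but each attainment model adjusts for one of them, which gives up a small amount of precision

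*Protocol article*

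**What the plan says.** Under Baseline measures, Attainment, the protocol states that "a baseline covariate will be derived from the raw test scores in Reading and Mathematics at Key Stage 2", and that these are "collected directly from schools before randomisation for each enumerated pupil in years 8 and 9 at September 2020". The Baseline data list under section 18a repeats this: "Raw test scores in Reading and Mathematics at KS2 for each enumerated pupil in Years 8 and 9 at September 2020".

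The general rule for choosing a covariate is that, where possible, "a pre-randomisation measure on the same outcome will be obtained in order to form a baseline covariate in the relevant analyses". The models follow it subject by subject:

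- **Primary analysis, Model 2** (the source of the headline effect size, with funder guidance cited): "with KS2 Reading raw score as a covariate expressed as a departure from the school mean for each pupil at the pupil level", plus the school mean.
- **Primary analysis, Model 3**: "As model 2, with additional covariates representing sex, month of birth, unauthorised absences in the year prior to randomisation and FSM variables". KS2 Mathematics is not among the additions.
- **Tables 3 and 4, English rows**: KS2 Reading at pupil and school levels.
- **Tables 3 and 4, Mathematics rows**: "KS2 mathematics raw score at pupil and school levels".

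No attainment model uses both scores.

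**The concern.** The trial holds two pre-randomisation measures of prior attainment and uses one at a time. The number of schools was set by recruitment and budget limits, and recruitment has closed, so the choice of covariates is one of the few remaining ways to gain precision. The protocol also expects that some schools may withdraw, while Table 2 computes detectable effects at the full 160.

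At stake is a smaller standard error and adjustment for any chance difference between arms in the part of prior attainment that the second score measures and the first does not. The validity of the treatment comparison is not at stake. Because the protocol names the covariates model by model, this is a choice already fixed, not a detail left open for the analysis plan.

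**Working it through.** **Inputs from Table 2 (SEND column).** School ICC 0.20; pre-test/post-test correlation 0.70 at pupil level and 0.32 at school level; 160 schools, 1:1; 25 SEND pupils per school; two-sided alpha 0.05; power 0.80. Squaring the correlations gives R² = 0.49 (pupil) and 0.1024 (school).

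**Formula.** With half the schools in each arm,

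MDES = M × √[ 4/160 × ( 0.20(1 − R²school) + 0.80(1 − R²pupil)/25 ) ],

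where M = t(0.975) + t(0.80) on 157 degrees of freedom = 2.819.

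**Step 1: reproduce the stated figure.**

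- Between schools: 0.20 × 0.8976 = 0.17952
- From pupils: 0.80 × 0.51 / 25 = 0.01632
- Sum: 0.19584
- MDES = 2.819 × √(0.025 × 0.19584) = 0.197, against 0.20 in Table 2

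The same formula gives 0.190 for all pupils and 0.194 for FSM pupils, both stated as 0.19. The planned figures stand.

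**Step 2: where the variance lies.** 0.17952 / 0.19584 = 92% of the residual variance of a school mean is between schools. Even a second score that removed all the remaining pupil-level variance would lower the MDES only to 0.189.

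**Step 3: add the second score.** The protocol gives neither the correlation of KS2 Mathematics with GCSE English nor that between the two KS2 scores. Assume that the second score predicts the outcome as well as the first at each level (0.70 and 0.32), and that the two scores correlate at r = 0.7 to 0.9 at both levels. With two equally predictive scores, R² = 2 × (correlation)² / (1 + r), so R²pupil = 0.98/(1 + r) and R²school = 0.2048/(1 + r). One further school-level degree of freedom is charged (156).

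| r (assumed) | R² pupil | R² school | Residual sum | MDES | Equivalent schools |
|---|---|---|---|---|---|
| 0.7 | 0.576 | 0.120 | 0.1895 | 0.194 | 165 |
| 0.8 | 0.544 | 0.114 | 0.1918 | 0.195 | 163 |
| 0.9 | 0.516 | 0.108 | 0.1939 | 0.196 | 162 |

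Equivalent schools = 160 × 0.19584 / residual sum. The gain is about 2 to 5 schools, and smaller if the cross-subject score predicts less well than the same-subject one.

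**Step 4: what a larger gain would need.** Holding pupil-level R² at 0.49, suppose that the second school mean explained a further 5%, 10% or 20% of the residual between-school variance. The MDES would be 0.193, 0.188 or 0.178. Explaining a further 2% to 20% of the pupil-level residual alone leaves it at 0.197 to 0.196. Nearly all further gain therefore depends on the school-level term, for which the protocol has no figure.

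**The case against.** The strongest reply is that nothing here is wrong. The protocol states a rule, a baseline measure of the same outcome, and applies it consistently. The planned MDES of 0.20 is met with that single pre-test. Prior attainment is already adjusted for at both levels, so only the part of the second score unrelated to the first is left out. That reply stands, and it limits the point to an efficiency improvement. It does not remove the point: the rule says that a same-outcome measure will be obtained, not that it must be the only one. Model 3 itself adds covariates that are not same-outcome measures.

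A second reply also stands. The headline effect size is tied to Model 2 by reference to funder guidance that is not at hand. If that guidance fixes a single pre-test, the headline estimate cannot change, and the improvement is confined to Model 3 and the secondary tables.

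Third, the addition is free only in data collection. Pupils without the other-subject score need a rule, and every attainment model gains an extra school-mean term.

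**Conclusion.** The point holds as a modest improvement. Both scores are held, no attainment model uses both, and adding the second would be expected to help slightly. On the stated assumptions, the SEND MDES moves from 0.197 to about 0.194–0.196, equivalent to about 2 to 5 schools. The calculation rests on Table 2's inputs and on an assumed equal predictive value and a between-score correlation of 0.7 to 0.9.

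Three stronger readings are tempting, and the protocol does not support them:

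- **That the primary estimate is biased or the model mis-specified.** Randomisation protects the estimate with either covariate set, and its standard error already reflects the unexplained variation.
- **That the loss is worth 20 or 30 schools.** Gains of that size need a school-level R² of about 0.20 to 0.25. With equally predictive scores, 0.20 requires r = 0.2048/0.20 − 1 = 0.02, and 0.25 requires r = 0.2048/0.25 − 1 = −0.18. Neither is plausible for two attainment scores averaged over the same pupils.
- **That Reading is a narrower score than the one behind the power calculation.** The sample size section refers to a "correlation between KS2 Raw score for English and GCSE English language attainment" while Model 2 names Reading. Whether these are different measures depends on a source that is not shown, and adding Mathematics would not settle it.

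**What to change.** Before outcome data arrive, add the other-subject KS2 raw score, as the pupil's deviation from the school mean plus the school mean, to:

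- Model 3 of the primary analysis (KS2 Mathematics);
- the English rows of Tables 3 and 4 (KS2 Mathematics);
- the Mathematics rows of Tables 3 and 4 (KS2 Reading).

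Pre-specify a missing-indicator rule for the added score so that no pupil is lost from the analysis. For example, set a missing score's deviation to zero, compute the school mean from the observed scores, and include the indicator. Extend the change to Model 2 only if the cited funder guidance permits more than one pre-test; otherwise leave Model 2 as it is.

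The cost is two covariate terms per model, about one school-level degree of freedom out of 157, and the missing-score rule. No new data are needed.

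### Missed precision gain: about 92% of the primary effect's sampling variance is between schools, but Model 2's only school-level baseline measure is assumed to explain about 10% of the between-school variance

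*Protocol article*

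**What the plan says.** The protocol article's Primary analysis section fits a two-level linear model to SEND pupils only and takes the effect size from Model 2, citing funder guidance. Model 2 holds the arm indicator, region fixed effects and KS2 Reading. KS2 Reading enters at pupil level as a deviation from the school mean, and "as a school average departure from the overall mean at the school level". Model 3 adds sex, month of birth, prior unauthorised absence and FSM. The attainment rows of Tables 3 and 4 also use KS2 at pupil and school level.

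Table 2 (Sample size {14}) assumes pre-test/post-test correlations of 0.70 for pupils and 0.32 for schools, 160 schools, and 25 SEND pupils per school. On clustering it says: "The assumption used for the intraclass correlation coefficient is 0.20 (proportion of the total variance at the school level". The resulting MDES is 0.20 for SEND pupils and 0.19 for all pupils and for FSM pupils.

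Baseline measures states the general aim that, where possible, "a pre-randomisation measure on the same outcome will be obtained in order to form a baseline covariate in the relevant analyses". The subsections that follow, and the Baseline data list under {18a}, name only items recorded pupil by pupil. Earlier GCSE results of the schools do not appear.

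**The concern.** In a trial that randomises schools, precision depends mainly on how many schools there are and how well differences between them are predicted. The first is settled: the Sample size section ties the school count to budget and recruitment, and Trial status says recruitment has ended. The second rests on one covariate with an assumed correlation of 0.32. Because the model is fitted to SEND pupils, that covariate is naturally read as a mean over about 25 children per school. It comes from a test taken at age 11, so it describes the intake more than the school's own performance at GCSE.

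The plan therefore adjusts well at pupil level, where little sampling variance lies, and lightly at school level, where most of it lies. What is at stake is the width of the confidence interval for the primary effect. The validity of the estimate is not in question.

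**Working it through.** **Inputs (Table 2 and Sample size {14}).** J = 160 schools; allocation 1:1, so P = 0.5; n = 25 SEND pupils per school in one year cohort; ICC ρ = 0.20; pupil R² = 0.70² = 0.49; school R² = 0.32² = 0.1024; two-sided alpha 0.05; power 0.80.

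**Formula (two-level cluster-randomised design).**

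Var = [ρ(1 − R²_school) + (1 − ρ)(1 − R²_pupil)/n] / [P(1 − P)J]

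MDES = M × √Var, with M = t(0.975) + t(0.80) on J − 1 − 2 = 157 degrees of freedom, which is 2.819.

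**Step 1: reproduce the plan's figure.**

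- School term: 0.20 × (1 − 0.1024) = 0.17952
- Pupil term: 0.80 × 0.51 / 25 = 0.01632
- Var = (0.17952 + 0.01632) / 40 = 0.004896; SE = 0.0700
- MDES = 2.819 × 0.0700 = 0.197, which rounds to the stated 0.20

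With n = 180 and n = 42 the same formula gives 0.190 and 0.194, matching the two stated values of 0.19. Reading 0.32 as an R² would give 0.174 for SEND pupils, so it is a correlation.

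**Step 2: where the variance lies.** School share = 0.17952 / 0.19584 = 91.7%. This is the share after the planned KS2 adjustment; with no covariates it is 86%. With unlimited pupils per school the MDES would still be 0.189. Leaving out the school-level KS2 term would raise it only from 0.197 to 0.207.

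**Step 3: what a better school-level predictor would do.** The school-level R² with an added covariate is not in the documents. The values below are assumptions. The first row is no gain.

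| Total school-level R² (assumed) | MDES | Equivalent schools under planned model | Power at 0.20 |
|---|---|---|---|
| 0.10 (as planned) | 0.197 | 160 | 81.5% |
| 0.15 | 0.192 | 168 | 83% |
| 0.20 | 0.187 | 178 | 85% |
| 0.30 | 0.176 | 200 | 89% |
| 0.50 | 0.152 | 269 | 96% |

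Equivalent schools = 160 × 0.19584 / [0.20(1 − R²) + 0.01632]. For R² = 0.30: 160 × 0.19584 / 0.15632 = 200. Power uses the normal approximation. The last row needs a multiple correlation of about 0.71.

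**Step 4: sensitivity to the ICC.** The protocol allows that 0.20 may be cautious. At ICC 0.15 the planned MDES is 0.174 and the school share 89%; at 0.10 they are 0.147 and 83%. The trial is then more precise, but the between-school part still dominates.

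**The case against.** The plan is consistent on this point: Model 2 and Table 2 make the same adjustment, and the MDES follows. An extra covariate can be called a reviewer's preference, and four parts of that case stand.

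- **The size of the gain is unknown.** What counts is how much earlier GCSE results add, given KS2, in predicting SEND pupils' marks. The new covariate would be a mean grade from different children, some years before the 2023 and 2024 outcomes. A reader might infer that the MDES would fall to about 0.15. The documents give no school-level R² that supports this.
- **No commitment is broken.** A reader might take the Baseline measures sentence as a promise the plan fails to keep. Its own subsections specify pupil-level measures, and an earlier cohort's grade is not a measure on trial pupils.
- **The data are not shown to be in hand.** A reader might infer that the data contractor already collects these results. The Outcome data section covers only trial pupils' GCSE results in 2023 and 2024, and schools outside the contractor's Aspire system have to be asked directly.
- **Funder guidance may fix Model 2.** If the covariate can go only into another model, the headline estimate gains nothing.

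It does not follow that the matter is a detail for the SAP or the full protocol. The article itself fixes the headline model, its covariates and the baseline data.

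**Conclusion.** The point holds as a missed gain in precision. Under Table 2's assumptions about 92% of the sampling variance of the primary effect is between schools after KS2 adjustment, and the only school-level baseline measure is assumed to remove about 10% of the between-school variance. Region effects are also in the model, but the MDES calculation credits them with no explained variance. With the number of schools fixed, better school-level prediction is the main lever left.

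The stated MDES of 0.20 is not wrong. The improvement could be nil, and for SEND pupils it may well lie near the low end of the table: at a total R² of 0.20 the MDES moves only from 0.197 to 0.187. A reader might also infer that a covariate recorded before randomisation can safely be added at any time. That is so only if the model is specified before outcome data are seen; choosing it afterwards could bias the result.

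**What to change.** Before any outcome data are seen:

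1. Request through the data contractor one value per school and subject: mean GCSE English and mean GCSE mathematics grade from a cohort before the 2020 closures.
2. Pre-specify the English value as an added school-level covariate in Model 2, and the matching subject's value in the attainment rows of Tables 3 and 4. Use a missing indicator for schools with no such cohort.
3. Optionally add the school KS2 mean over all enumerated pupils, whose scores are already collected.
4. Report the planned Model 2, without these terms, as a sensitivity analysis. If funder guidance fixes Model 2, report the augmented model as a named adjusted analysis and accept that the headline MDES stays at 0.20.
5. While editing, reconcile the Additional baseline data items section with Model 2: it describes an analysis with the baseline at pupil level only, whereas Model 2 uses both levels.

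Cost: one extra school-level field per subject, with a direct request to schools outside Aspire, and a check that the data-sharing agreement covers it. In each model the grade and its missing indicator use one or two degrees of freedom, and the all-pupil KS2 mean would use one more, out of about 157.
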